### Randomization and allocation concealment

Randomization of participants was performed using a computer to generate random numbers. After assignment of random numbers to the 72 consenting participants, the list was sorted based on the random number. Thirty-six participants in the upper rank were assigned to the intervention group (NEO-MOM) and the remaining 36 participants were assigned to the comparison group. Because of the nature of the intervention, blinding for both researchers and participants was not possible. The assessor was blind to the intervention condition for baseline and evaluation data collection.

### Behavioral based nutrition education

Social Cognitive Theory (SCT) was the underlying framework of the study, which focuses on behavior change through reciprocal determinism that incorporates interplay of person, environment and behavior [19]. Bauman, Sallis, Dzewaltowski, and Owen [20] argue that mediating factors lie in the behavior change pathway. In the present study, maternal behavioral change related to overweight/obesity may be influenced by self-efficacy for including more fruits and vegetables in the family menu, and for including more animal protein in their children’s diet for improved iron intake and growth. The behavioral mediators are a part of the personal component in SCT’s reciprocal determinism. The core concept of SCT is the importance of others in shaping people’s behavior. Nutrition education materials, including booklets for all participants, were developed based on the constructs of Social Cognitive Theory (SCT) (Fig. 2). This study addressed several means of enhancing maternal self-efficacy such as mastery of making a healthy menu, peer group modeling of child feeding practices or engaging physical activity and inducing desire to include fruits and vegetables in daily meals.

**Fig. 2 Fig2:**
[figure not shown]
Construct of NEO-MOM Intervention Based on Social Cognitive Theory

Because the problem of maternal-child double burden of malnutrition includes two opposing nutritional problems, the target behaviors for this project addressed both childhood stunting and maternal overweight/obesity. For mothers, the target behavior was consumption of fruits and vegetables, which both play a critical role in efforts to prevent overweight/obesity. For the child, the target behavior was increased consumption of animal protein as well as fruit and vegetables.

Manuals published in Bahasa Indonesia or in English in the last five years were identified to improve maternal fruit and vegetables intake as well as to increase child intake of animal protein. Both peer-reviewed articles and gray literature were located and translated into Bahasa Indonesia. Manuals were drafted and refined through a lengthy review process and will be used as the printed educational materials for the intervention.

### Training community health workers

One month before the intervention, community health workers received training on motivational interviewing, a collaborative, goal-oriented style of communication commonly used to promote behavioral change in health care [21]. It is designed to strengthened personal motivation for and commitment to a specific goal by eliciting and exploring the person’s own reason for change within an atmosphere of acceptance and compassion. The core skills of motivational interviewing consist of open questions, affirmations, reflections and summaries. Community health workers will use motivational interviewing during biweekly home visits in the intervention group to give verbal encouragement and find ways to overcome potential barriers for mothers to achieve their goals. The training program took a full day to complete, and was led by study investigators. The training involved a combination of didactic learning, role-playing, and case study discussion.

### Intervention

All participants (NEO-MOM and PRINT Group) received six sets of educational materials in the form of booklets that described strategies to improve the health of stunted children and overweight mothers in alignment with constructs of Bandura’s Social Cognitive Theory (SCT). In addition, mothers were provided with grocery vouchers after consenting to participate in the study during the baseline and evaluation phase. The voucher is worth about USD $1.50, or about IDR Rp. 30,000, and can only be used in designated grocery stores to buy foods and not for alcohol or tobacco.

The intervention group or NEO-MOM group received six sessions of behaviorally based nutrition education focusing on healthy food choice and child feeding practices, along with six sessions of motivational interviewing provided through home visits by a trained community health worker. Mothers were given a biweekly grocery voucher every time they attend a nutrition education session as an appreciation for their time and commitment to the study. The session was conducted on a biweekly basis. In total, the intervention spanned three months. The approximate duration of each nutrition education session was 100 min, consisting of a 50-min class session, followed by a hands-on activity lasting 50 min. The session was administered to mothers with children being allowed to attend and sit with their mothers. Research assistants and community health workers were present during the session to help handle the children when necessary. During the nutrition education sessions, hands-on activities were provided to help mothers improve their self-efficacy toward dietary diversity, healthy eating, and child feeding. These activities were designed to enable mothers to cope with basic household and environmental obstacles. The content of the six sessions of nutrition education are outlined in Table 1.

**Table 1 Tab1:** Intervention Components of NEO-MOM

Construct of Social Cognitive Theory	Behavior mechanism impacted	Session	Intervention components
Provide information on health risk of maternal overweight/obesity and child stunting	Mechanisms affecting belief formation/cognitive mechanisms toward maternal nutrition literacy	Session 1	50-min nutrition education class on the introduction on the double burden of malnutrition, especially consequences and management of overweight/obesity and child stunting.
Outcome expectation	By improving maternal nutrition literacy, mothers might expect a healthier child (their child not stunted) and improved maternal nutritional status (not overweight/obese).	Session 3	50-min nutrition education class on Indonesian balanced diet and Indonesian version of MyPlate followed by healthy behavior message to improve maternal fruit and vegetable consumption, serve more animal protein to their child and increase maternal daily steps.
Environment (food access, peer support)	With supportive environment, it will be easier to perform the intended healthy behavior.	Session 1–6	Mothers in intervention group gathered every two weeks during nutrition education class to provide bonding and peer support. Access to food increased by distributing a grocery voucher every time mothers in the intervention group attended the nutrition education session.
Mastery experience	Performing intended behavior during nutrition education class or during the hands-on activities session will improve maternal self-efficacy for performing the following behaviors: 1. Healthy grocery shopping 2. Food preparation 3. Physical activity	Session 2 Session 1–6 Session 3 Session 4	50-min nutrition education class on healthy grocery shopping followed by a 30-min mock grocery shopping session. 20-min dance session 30-min making menu for children under five years old with emphasis on including animal protein (chicken liver, catfish or eggs). 30-min nutrition education class on healthy cooking methods followed by a 60-min cooking demonstration.
Goal setting	Assisted planning and goal setting will make behavior change perceived as attainable by mothers.	Session 1 Session 6	30-min hands-on experience on goal setting to improve physical activity (as in daily steps), maternal fruit and vegetable intake and serving animal protein to their children. 50-min Focus Group Discussion (FGD) on how to overcome barriers towards child feeding practices followed by 30 min creating a pledge and strategies for tackling stunted child and overweight/obese mother (SCOWT) from the mother’s own perspective.
Vicarious experience	Watching video of how others perform responsive feeding, maternal self-efficacy for preparing more animal protein will improve.	Session 5	50-min nutrition education class on child feeding practices with emphasis on responsive feeding.
Verbal Motivation	Verbal motivation from a respected informal leader such as community health worker will improve maternal self-efficacy for: 1. Healthy grocery shopping 2. Food preparation 3. Physical activity	Home visit Session 6	The motivational interviewing delivered through home visit (six times throughout the study administered on alternate weeks from nutrition education class and hands-on activity sessions) will focus on providing verbal motivation for mothers to achieve their biweekly goals (consisting of improving daily steps, increasing maternal fruit and vegetable intake, and serving their child animal protein), and help with strategies to overcome barriers. 30-min of role playing and jingle/song making related to combating child stunting.

The nutrition education classes were administered by three investigators in Indonesia with expertise in nutrition and behavioral change intervention who are on the faculty of the Department of Nutrition, Universitas Airlangga. All of the investigators hold a master’s degree in public health or community nutrition. The hands-on experience session was delivered by two trained research assistants who each hold a bachelor’s degree in public health nutrition.

The motivational interviewing was delivered through home visits, which took place six times throughout the study, administered on alternate weeks from nutrition education class and hands-on activity session. The visits focused on providing verbal motivation for mothers to achieve their biweekly goals, which centered on improving daily steps, fruit and vegetable intake, and serving child meals with animal protein, and helping them with strategies to overcome barriers. Each motivational interviewing session lasted for approximately 1 h. The motivational interviewing session took place during a home visit and was delivered by a trained community health worker living in the participant’s area.

### Comparison group: usual care plus print educational materials

The comparison group did not receive nutrition education or home visits by a community health worker. Participants in the comparison group received sets of printed educational materials, coupled with benefits from a government food supplementation program. The sets of printed educational materials (booklets) were provided after baseline data measurement for both intervention and comparison group. Printed material was chosen as the medium for source of information due to several considerations: to mimic government strategy for distributing the health messages through the “Kartu Menuju Sehat” (KMS) or a child’s growth monitoring card and because it was deemed unethical not to provide anything for participants knowing they had double burden of malnutrition in the form of SCOWT. Finally, these materials were provided to minimize the threat to internal validity that might occur. By providing the comparison group with the same printed educational materials, we aimed to avoid resentful demoralization of participants in the comparison group. All mothers participating in the study received usual care in the form of monthly growth monitoring of their child’s nutritional status at *posyandu* and access to a supplementary feeding program from Indonesian government. Supplementary feeding program was given for children under 5 years old that consist of foods equivalent with 1000 to 1550 kcal total energy and 25–39 g protein [22].

### Primary outcome

Outcome measurements were taken at baseline and at the end of the study (after three months). The primary outcome, on which power was calculated, is the change in child’s height (cm). Details of height measurement are found within the anthropometric data section below. The same methods of height assessment were used at baseline and subsequent measurement periods.

### Secondary outcomes

Secondary outcomes for this study consist of variables from anthropometric data, lifestyle data, and psychological data.

#### Anthropometric data

The secondary outcome measured in this study was maternal overweight/obesity and child stunting or the double burden of malnutrition measured as SCOWT. Data were collected on child’s age, weight and height, as well as maternal weight, height, and waist circumference. Weight was measured in light clothing, without shoes or sandals, on a Camry EB6571 digital scale (Guangdong, China) to 0.01 kg for weight. Height was measured to the nearest 0.1 cm using a stadiometer (SECA 213). Maternal weight and height measurement were used to calculate BMI. Waist circumference was measured horizontally halfway between the lowest rib and the upper prominence of the pelvis using a non-extensible steel tape (MyoTape) placed against the bare abdomen. We measured the change in maternal body mass index (BMI) and child height for age z-score (HAZ) as the secondary health outcome using the 2005 WHO reference standard to assess maternal and child nutritional status. All measurement will be done and recorded twice to ensure the validity. The third measurement will be taken if the difference between the prior two measurement differ by more than 1 %.

#### Lifestyle data

A household dietary diversity questionnaire was used to estimate maternal fruit and vegetable intake as well as the child’s animal protein intake [23]. The 24-h dietary recall was completed for two days, with one day in between the two. The secondary variables measured were total energy intake, total protein intake and total fat intake for the mother. The 24-h recall interviews were performed by research assistants. They were trained before the interview to follow a standardized protocol to ask neutral probing questions to encourage recall of food items and to teach different methods of food preparation and brands available in different cultures. Dietary data were analyzed using food processor software drawing from a database of Indonesian Food updated yearly by the Department of Nutrition, *Universitas Airlangga* (UA) – Indonesia. Actual spending of the voucher was evaluated in collaboration with the local grocery store recording each participant’s grocery shopping behavior. Maternal physical activity was measured in total daily steps using the Yamax Digiwalker Pedometer SW200 (Tokyo, Japan). Even though pedometer was less robust than accelerometer, this device is still regarded as an objective measure of physical activity in the previous study [24]. Mothers wore the pedometer for three consecutive days from each time point of measurement at baseline, 3 months, 6 months and 12 months evaluation. We generated a wear-time log for each mother to estimate time worn to arrive at a true daily step count.

#### Psychological variables

Outcome expectations about the targeted behavior of maternal fruit and vegetable intake as well as maternal physical activity and animal protein fed to their child were measured using the 30-item questionnaire adapted from several sources [25–27]. Sedentary behavior and sitting time were assessed using the last 7-d sedentary behavior questionnaire (SIT-Q-7d) [28]. Maternal self-efficacy to engage in physical activity was measured using a 10-item questionnaire on barriers to self-efficacy and an 8-item questionnaire on self-efficacy of performing the task. Maternal self-efficacy toward fruit consumption was measured using a 6-item questionnaire on barriers to self-efficacy and a 6-item questionnaire on performing the fruit consumption task. Maternal self-efficacy toward vegetable consumption was measured using an 8-item questionnaire on barriers to self-efficacy and an 8-item questionnaire on performing the vegetable consumption task. Maternal self-efficacy in serving and feeding their child animal protein will be measured using a 10-item questionnaire on barriers to self-efficacy and a 15-item questionnaire on performing the task of serving and feeding their child animal protein. All of the self-efficacy questionnaires were developed as Likert scale answers based on Bandura’s guide for constructing self-efficacy scales [29]. For all psychological variable we tested the Cronbach alpha prior to data analysis to test the internal consistency.

#### Moderating variables

Moderating variables such as age, child’s gender, family size, occupational status, educational attainment, nutritional literacy and food insecurity were collected through structured face-to- face interviews at the baseline. Number of children, household income, and food expenditure were used to estimate socioeconomic status (SES). Food insecurity was measured using the Household Food Insecurity Access Scale (HFIAS) guidelines [30].

### Process evaluation

To provide a sense of the quality of the outcomes to be measured, we conducted several measures of “process evaluation”. First, we monitored adherence to the intervention by making a log of nutrition education sessions including an attendance list filled by our research assistants in the form of biweekly goal-setting sheets completed by mothers at the end of class and following hands-on activity sessions. Through collaboration with the local grocery store, we monitored maternal grocery purchases from the recorded grocery voucher given to mothers each time they attended the class and hands-on session. In addition, a log of daily steps was recorded as a part of the motivational interviewing session with the community health worker during the home visit. Fidelity to the messages and curriculum was monitored by our research assistant that presented at the nutrition education classes, and also from the verbal report and feedback given by the community health workers to our research assistant after the home visit.

### Statistical analysis plan

We conducted a meditational analysis to examine whether changes in behavioral and psychological factors of the SCT construct (self-efficacy, outcome expectation and goal setting) mediated the association between the intervention and outcomes. Subgroup analysis was used to examine whether the association between the intervention and the outcomes were modified by socioeconomic status (SES), and demographics measured at baseline, such as age, number of children, educational status, employment, and nutritional literacy.

For all variables that are normally distributed or transformed to normality, we analyzed the difference in the outcome between the control and intervention group using a mixed factorial ANOVA. We used the household food insecurity access scale (HFIAS) score as covariates in the analysis. Furthermore, we conducted the ANCOVA test to see the difference in changes of primary and secondary outcomes adjusted for baseline value and the HFIAS score. For nonparametric statistics, we employed the two related-samples Mann Whitney U test and analyzed the data separately for the NEO-MOM group and the PRINT group with Bonferroni correction. All data analyses were performed in IBM SPSS Statistics 22 (Armonk, NY). The statistical significance for all tests was set at an alpha level of 0.05. In the event that after a follow-up of the intervention, the study has high noncompliance or missing outcomes, we planned to conduct an intention-to-treat (ITT) analysis.

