### Target population

The sample was drawn from community health posts *(“posyandu”)* [16] listing more than 50 mothers with children under the age of five. Informed consent was gathered from all participants before undergoing screening to validate their eligibility for participation. The case definition included overweight/obese mothers (BMI > 25) with stunted children (HAZ < -2). A BMI cut-off point of >25 kg/m2 was used to determine maternal overweight and obesity, while child stunting was defined as HAZ < -2, according to the child growth standard from the WHO-Anthro 2005. Repeated anthropometric measurement for both mothers and children are performed by trained research assistance in *posyandu*. A third measurement was initiated when the discrepancy between the first and the second measurement was greater than 1 %. An average of anthropometric measurements was used to determine eligibility. Following screening via anthropometric measurement, those eligible were invited to participate in the study.

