### Power calculation

The power calculation of the main outcome variable was based on a previous RCT in Bangladesh that explored effects of a similar three-month nutrition education intervention with complementary feeding on child’s height gain [17, 18]. Although the study did not directly provide complementary feeding, one of the inclusion criteria was that participants would be eligible to take part in a complementary feeding program administered by the government of Indonesia. The effect size of providing complementary food and intensive nutrition education on height gain (cm) in Bangladesh was 0.80 (95 % CI = 0.007–1.53). We selected this fairly large effect size of 0.8 expressed as mean difference in child height, which translates to an ability to detect a difference between two groups of 0.80 cm in child height at a three-month follow-up. The study has a 90 % power to detect modest changes at the individual level that would have an important impact if occurring at the population level. A minimum total sample size of 66 was needed to detect these differences in our primary hypothesis, with two-tailed alpha of 0.05. Assuming a dropout rate of 9 %, the total sample size of 72 was required (36 in the intervention group and 36 in the comparison group/usual care).

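### Normality of the variable, on a quantity the plan does not name, selects the analysis, and the stated alternative is a within-arm rank test that gives no treatment comparison

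*Protocol article*

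**What the plan says.** Three statements in the protocol article's Statistical analysis plan matter here.

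- The mixed factorial ANOVA is conditional on distribution: "For all variables that are normally distributed or transformed to normality, we analyzed the difference in the outcome between the control and intervention group".
- A separate sentence adds the adjusted model: "we conducted the ANCOVA test to see the difference in changes of primary and secondary outcomes adjusted for baseline value and the HFIAS score". It states no normality condition of its own.
- The alternative is: "we employed the two related-samples Mann Whitney U test and analyzed the data separately for the NEO-MOM group and the PRINT group", with a Bonferroni correction.

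The section does not say which quantity is checked for normality: baseline value, three-month value, change or residual.

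Two other sections bear on this. Target population sets the entry cut-offs: "The case definition included overweight/obese mothers (BMI > 25) with stunted children (HAZ < -2". Anthropometric data defines the related outcomes as changes: "We measured the change in maternal body mass index (BMI) and child height for age z-score (HAZ) as the secondary health outcome".

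**The concern.** The rule uses the wrong criterion. A linear model compares arms validly when its residuals are roughly normal; the marginal shape of the outcome or of a baseline covariate does not settle that. In this trial the two can part company, because the entry cut-offs keep only one tail of BMI and one tail of HAZ.

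The alternative route makes this matter. A related-samples test within each arm asks whether that arm changed. It does not estimate the difference between arms, and it adjusts for neither baseline nor HFIAS. The sample size was set for a between-arm quantity: "We selected this fairly large effect size of 0.8 expressed as mean difference in child height". An outcome analysed only by the within-arm route leaves the superiority question unanswered for that outcome. And when a data-dependent check chooses the test, the analysis can be settled after the data are seen.

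**Working it through.** **Sample size used in the check.** Power calculation gives an effect of 0.8, 90% power, two-sided alpha 0.05 and a total of 66 before dropout. No SD is stated; an SD of 1.0 cm is assumed because it reproduces the total. n per arm = 2 × (1.960 + 1.282)² × 1.0² / 0.8² = 32.8, rounded up to 33, total 66. This agrees with the plan and is not in dispute. It supplies N = 66 below.

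**Does truncation at entry affect the quantity checked?** The inputs from the document are the cut-offs, BMI > 25 and HAZ < -2. The rest is assumed, because the document gives no distributions:

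- BMI: normal population, mean 23 to 29, SD 4, truncated at 25.
- HAZ: normal population, mean -2.5 to -1.0, SD 1.0 to 1.3, truncated at -2.
- Three-month value = baseline + change. Change is normal with mean 0, independent of baseline, SD 0.5 to 1.0 (BMI) or 0.2 to 0.4 (HAZ).
- Check: Shapiro-Wilk at 0.05, 1,000 samples per setting. The plan names no test; this one is an assumption.

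The model for the residuals was change = a + b × arm + c × baseline, with no true arm effect and HFIAS omitted.

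| Quantity checked | BMI: samples failing | HAZ: samples failing |
|---|---|---|
| Baseline value | 66-100% | 90-100% |
| Three-month value | 39-95% | 33-91% |
| Change | 4-6% | 4-6% |
| ANCOVA residual | 4-6% | 4-6% |

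Baseline skewness was about 0.6 to 1.2 for BMI and -0.8 to -1.3 for HAZ. The type I error of the ANCOVA was 4.4-6.1%. With 1,000 runs the Monte Carlo standard error at 5% is √(0.05 × 0.95 / 1,000) = 0.7 points, so these are consistent with 5%. The ANCOVA on change is sound in exactly the settings where a check on raw values usually fails.

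**Can transformation rescue the raw values?** At baseline, the square root of the distance from the cut-off lowered failures to 6-16%; the log of that distance did not help (92-99%). The square root is undefined for anyone who crosses the cut-off by follow-up, which is what the intervention aims for. Even with no treatment effect, under similar assumptions (BMI mean 23 to 28, SD 4; HAZ mean -2 to -1.4, SD 1.1 to 1.2), at least one participant crossed in 75-100% of samples of 66. HAZ is negative, so an ordinary log or square root is not available.

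**What does the within-arm route deliver?** Suppose both arms truly change by the same amount, and each within-arm test is significant with probability p. With independent arms, the chance that exactly one is significant is 2p(1 - p). At p = 0.025 this is 2 × 0.025 × 0.975 = 4.9%; at p = 0.5 it is 2 × 0.5 × 0.5 = 50%. A significant result in one arm only is therefore no evidence of a treatment effect, and a Bonferroni correction, which only lowers p, does not turn it into one.

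**The two readings of the ANCOVA sentence.**

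1. It continues the parametric branch, since it sits between the normality condition and the nonparametric sentence. Outcomes that fail the check then have only the within-arm test.
2. It stands alone. Outcomes that fail then have an ANCOVA and a within-arm test, with nothing to say which is the result.

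**The case against.** The strongest reply is that the normality clause is attached to the mixed ANOVA, while the ANCOVA covers changes in primary and secondary outcomes without a stated condition. The outcomes are themselves defined as changes, and the cut-offs truncate the screening value, not the change. This stands. A reader might infer that BMI and HAZ are bound to lose the adjusted ANCOVA, or that the analysed changes are non-normal by design. The text supports neither: the first follows only under one reading, and the simulated changes fail at about 5%. Nor does the spread of the children's ages decide the route for the primary outcome, which is change in height.

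It is also fair that the plan names no normality test, and that a condensed article may leave such detail to a fuller document. But the selector and the within-arm alternative are both stated here, and neither is a detail left open. A mixed factorial ANOVA takes baseline and follow-up values as its inputs, so checking raw values is the natural reading, though not the only one.

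Finally, the loss would be small if the alternative were a between-arm rank test on change. In simulated trials of 33 per arm with an effect of 0.8 residual SD, such a test had 85-87% power against 88-89% for ANCOVA. The plan, however, specifies a within-arm analysis. The name it gives the test is contradictory, since Mann-Whitney is a test for independent samples, but running it separately in each arm leaves no between-arm comparison.

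**Conclusion.** The point holds as a cheap improvement to a stated rule. The plan lets an unspecified normality check choose the analysis, on a criterion the linear model does not require, and its alternative cannot test the treatment effect. BMI and HAZ are the outcomes most exposed: if raw values are checked, failure is common (33-100% across the settings above), although the ANCOVA on change is valid.

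The percentages rest on assumed population values, a sharp cut-off at baseline and a normal change unrelated to baseline. Baseline was measured in the home after screening at the health post, so the real truncation may be somewhat blurred. A skewed change would raise the residual failure rate, but not because of the entry criteria. The conclusion that the selector should go does not depend on the exact figures, and both readings of the ANCOVA sentence lead to the same correction.

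**What to change.** Remove normality of the variable as the selector. State that the between-arm comparison for every continuous outcome is the ANCOVA on change already planned, with baseline value and HFIAS score as covariates. Check its residuals; if they are clearly non-normal, keep the same estimate and report a robust-standard-error or permutation p-value. Any transformed or rank analysis becomes a sensitivity analysis, and a rank analysis should compare the arms with each other.

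The cost is a sentence or two of wording and no new data. The downside is some loss of efficiency for very skewed outcomes, such as dietary intake or daily steps, where a between-arm rank test may be more powerful than a mean difference.

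### Two overlapping between-group tests (mixed ANOVA and baseline-adjusted ANCOVA) are each run at 0.05 on the same parametric outcomes, and neither is named as the result

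*Protocol article*

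**What the plan says.** All of this is in the protocol article, mainly under Statistical analysis plan.

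- **First model.** For variables that are normal or transformed to normality, "we analyzed the difference in the outcome between the control and intervention group using a mixed factorial ANOVA". On covariates: "We used the household food insecurity access scale (HFIAS) score as covariates in the analysis". The baseline value is not named as a covariate of this model, and the text does not say which ANOVA term is read.
- **Second model.** "Furthermore, we conducted the ANCOVA test to see the difference in changes of primary and secondary outcomes adjusted for baseline value and the HFIAS score".
- **Threshold.** "The statistical significance for all tests was set at an alpha level of 0.05". The only multiplicity correction belongs to the nonparametric route, where the authors "analyzed the data separately for the NEO-MOM group and the PRINT group with Bonferroni correction".
- **Ranking.** Neither parametric model is called primary, confirmatory, supportive or sensitivity.
- **Timing.** The Primary outcome section and the design overview give two occasions, baseline and 3 months. Under Lifestyle data, pedometer steps are listed at four: baseline, 3, 6 and 12 months.
- **Sample size.** The Power calculation section uses 90% power "with two-tailed alpha of 0.05" and is tied to neither model.

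**The concern.** When an outcome is measured once before and once after treatment, the time-by-group term of a mixed ANOVA is algebraically the comparison of mean change between arms. The ANCOVA of change on arm and baseline value estimates the same treatment effect, but lets the data set the weight given to baseline instead of fixing it at one. The plan therefore asks one question twice, at full alpha each time, and does not say which answer counts if the two differ.

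Two things follow. A result can be called significant if either test crosses 0.05, so the error rate per outcome exceeds 5%. And if the ANOVA is taken as the answer, precision is lost wherever baseline and follow-up are only weakly correlated. That is plausible for dietary recall, self-efficacy, sitting time and step counts, which carry the secondary hypotheses.

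**Working it through.** **1. The plan's own figure.** With a two-sided alpha of 0.05, 90% power and a difference of 0.8 SD (SD taken as 1, since none is stated):

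n per arm = 2 × (1.960 + 1.282)² / 0.8² = 2 × 10.51 / 0.64 = 32.8, rounded up to 33, or 66 in total.

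This matches the stated 66, and 66 × 1.09 = 71.9 gives the stated 72. The calculation is a plain two-group comparison of means and does not show which model was intended. The checks below use 33 per arm.

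**2. Relative precision.** Let both occasions have variance σ² and correlation r (assumed; the documents give none). Per child:

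- change-score variance: 2σ²(1 − r)
- ANCOVA residual variance: σ²(1 − r²)
- ratio, change score to ANCOVA: 2 / (1 + r)

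**3. Overlap of the two tests.** Under no effect, the covariance of the two estimates is proportional to 1 − r². Their correlation is (1 − r²) / √[2(1 − r)(1 − r²)] = √[(1 + r)/2]. Putting this into a bivariate normal gives a large-sample chance that at least one of two 0.05 tests is significant.

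**4. Simulation.** Each r was run with 30,000 null trials and 6,000 trials with an effect of 0.8 residual SD, 33 per arm, with HFIAS in both models. The Monte Carlo standard error for the null rates is about √(0.077 × 0.923 / 30,000) = 0.15 percentage points.

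| Assumed r | Variance ratio 2/(1 + r) | Correlation of tests | At least one false positive, simulated | Same, large-sample | Power, change score | Power, ANCOVA |
|---|---|---|---|---|---|---|
| 0.3 | 1.54 | 0.81 | 7.7% | 7.8% | 72% | 89% |
| 0.5 | 1.33 | 0.87 | 7.5% | 7.3% | 78% | 89% |
| 0.7 | 1.18 | 0.92 | 6.5% | 6.8% | 84% | 89% |
| 0.99 | 1.005 | 0.998 | 5.3% | 5.3% | 89% | 89% |

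Another simulation, with 20,000 null trials per r, gave 7.7, 7.3, 6.6 and 5.2%. Used alone, the ANCOVA had a simulated error rate of 4.8 to 5.2%.

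**5. Where each row applies.** A child's height three months apart is almost perfectly correlated, so the last row is the relevant one (an assumption, but a safe one). The first three rows are a plausible range for behavioural and psychological measures.

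**The case against.** **The primary outcome is hardly touched.** This stands. Change in child height is the only outcome on which power was calculated. At r near 0.99 the two tests almost always agree and have the same power.

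**The larger figures rest on assumed correlations.** This also stands, which is why a range is shown. The rise to about 7% is modest, and these secondary outcomes are numerous with no stated multiplicity control in any case.

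**A condensed article may leave ranking to a fuller plan.** This stands in part. Missing detail alone would not be a point. But the article does more than stay silent: it commits to both tests and sets 0.05 for each. The word that introduces the ANCOVA could be read as making it supplementary, but the text does not say so, and that reading would leave the less precise test as the main one.

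**Not every outcome is affected.** Correct. SCOWT status is binary, non-normal variables take another route, and a mixed ANOVA of steps over four occasions would not duplicate a 3-month ANCOVA.

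**Stronger readings the documents do not support.**

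- A reader might infer a 9.75% error rate (1 − 0.95²). That needs independent tests, and these are strongly correlated.
- A reader might take the ANOVA sentence to mean the group main effect. That term averages in the baseline value, so 0.8 cm becomes 0.4 cm, set against the full between-child variance. With an assumed SD of 5 to 7 cm and r of 0.98 to 0.99, power would be about 6%. The article never says this term is used, and the primary outcome and secondary hypotheses are framed as change. The figure shows only why the term should be named; it is not a defect of the plan as written.

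**Conclusion.** The point holds for continuous outcomes analysed parametrically and measured at baseline and 3 months. For those, the plan fixes two tests of one effect at 0.05 each and designates neither. The resulting error rate per outcome is about 6.5 to 7.7% at assumed correlations of 0.3 to 0.7. Over the same range, the change-score test carries 54% down to 18% more variance than the ANCOVA. At r = 0.3 its power is 72% where the ANCOVA has 89%.

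For child height the consequence is negligible: about 5.2% error and a variance difference of 0.5%. The conclusion on height does not depend on which model is chosen, provided the time-by-group term is the one read. These sizes assume equal variances on the two occasions, normality and 33 analysed per arm. The issue is worth correcting because the better test is already in the plan, but it does not threaten the primary comparison.

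**What to change.** Name one analysis. For each continuous outcome analysed parametrically, the 3-month between-group result is the arm coefficient, with 95% CI, from an ANCOVA on arm, baseline value and HFIAS score. The dependent variable may be the 3-month value or the change; with baseline in the model the arm coefficient is identical. Label the mixed factorial ANOVA descriptive or supportive, and state that only its time-by-group term is read.

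Reconcile the pedometer schedule under Lifestyle data with the two-occasion design given elsewhere. If steps are in fact measured at 6 and 12 months, keep a baseline-adjusted repeated-measures analysis for those visits, so that they are not left without a planned test.

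The cost is wording only, with no new data, participants or model, as long as the choice is made before the outcome data are seen. The section is written mostly in the past tense. If the analyses had already been run, the designation should be declared post hoc and both results reported for every affected outcome.
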